### Recruitment

To control the effect of age, we will use 65-year-old cut-off considered as the conventional threshold for cardiovascular disease risk as indicated by the literature review of clinical trials. We aim to stratify participants based on relevant biological variables (e.g., age and sex) and secure a balanced representation of diverse demographic groups, thereby increasing the generalizability of our findings. Cardiovascular dysfunction becomes particularly prominent at neurological levels ≥T6. Such impaired control of the heart rate and blood vessels elevates ischemic risks and damages endothelial cells within the vessels, and fosters various vascular diseases, leading to increased mortality risk following SCI. Thus, our target population is 18–65-year-old adults with AIS A–C ≥ T6.

All subjects will be recruited from the inpatient rehabilitation program at the HMC. The screening will begin prior to admission to the inpatient rehabilitation program. The research assistant will follow the physicians’ referral for any potentially eligible patients. Those patients identified as potentially eligible will be approached in person by research study staff (coordinator or research assistant) in their hospital room during their first week of inpatient rehabilitation and request permission to both screen for and discuss the study based on approved screening form. People interested in volunteering will be evaluated for eligibility by one of the investigators and medical coordinators. Candidate participants will be asked for their oral consent to receive the screening questionnaires. This includes a yes-no questionnaire and multiple-choice questions in person. Inclusion and exclusion criteria are outlined in Table 1.

**Table 1 pone.0347211.t001:** Participant inclusion and exclusion criteria.

Inclusion criteria	Exclusion criteria
Are between 18–65 years of age. SCI (non-progressive) at or above the T6 spinal segment. Admitted to inpatient rehabilitation units or discharged from inpatient rehabilitation units but within 4 months since the onset of injury. American Spinal Injury Association Impairment Scale (AIS) A or B, or C for SCI. Have a stable medical condition that would permit participation in testing activities. Willing and able to comply with all clinic visits and study-related procedures. Able to understand and complete study-related questionnaires in English. Have no painful musculoskeletal dysfunction, unhealed fracture, pressure sore, or active infection that may interfere with testing. Are not currently pregnant or not intending to become pregnant during participation in this study. Are volunteering to be involved in this study. Must provide informed consent.	Autoimmune etiology of spinal cord dysfunction/injury. History of additional neurologic disease, such as stroke, MS, etc. Rheumatic diseases. (rheumatoid arthritis, systemic lupus erythematosus, etc.) Ventilator dependent. Clinically significant, unmanaged, depression, ongoing alcohol and/or drug abuse that interfere with study participation. Use of any medication or treatment that in the opinion of the investigators indicates that it is not in the best interest of the participant to participate in this study. Intrathecal baclofen pump. Cardiovascular, respiratory, bladder, or renal disease unrelated to SCI or presence of hydronephrosis or presence of obstructive renal stones. Presence of severe acute medical issues that in the investigator’s judgment would adversely affect the participant’s participation in the study. Examples include, but are not limited to acute urinary tract infections, debilitating pain, pressure sores, or unstable diabetes. Presence of pacemakers, stimulators, or medication pumps in the trunk, deep brain stimulators, metallic devices in the head such as aneurysm clips/coils and stents, or vagus nerve stimulators. A member of the investigational team or his/her immediate family. History of severe allergy. Malabsorption syndrome, primary hyperthyroidism, or hypogonadism. History of seizures.

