## Background

Recent global estimates indicate that approximately one million new spinal cord injuries (SCI) occur each year, and more than 20 million individuals are living with SCI [1]. While paralysis is widely recognized as the most apparent and debilitating consequence of SCI, cardiovascular dysfunction is consistently reported as a leading health concern and the primary cause of mortality in this population [2–5]. Injuries at or above the level of sixth thoracic spinal cord segment (≥T6) disrupt descending supraspinal sympathetic control [6]. Loss of sympathetic outflow compromises vascular tone, which is essential for maintaining of arterial blood pressure [7].

Following SCI, the autonomic nervous system enters a state of neurogenic shock due to the loss of descending tonic sympathetic control and the dominance of parasympathetic activity [8]. Neurogenic shock typically lasts days to weeks following the injury onset [9]. During neurogenic shock, individuals with SCI experience profound hypotension and bradycardia, often requiring vasopressor support [10]. Although neurogenic shock itself eventually resolves, cardiovascular instability frequently persists beyond the acute phase because of loss of supraspinal regulation of autonomic spinal cord circuits below the lesion [11]. This impaired control manifests by variety of cardiovascular dysfunction including orthostatic hypotension, characterized by blood pressure (BP) reductions during postural changes [12], and autonomic dysreflexia, marked by excessive hypertension in response to visceral stimuli such as bladder and bowel distension [13]. Both orthostatic hypotension and autonomic dysreflexia can cause rapid and severe BP changes that are life-threatening [14].

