### Sample size

We aim to recruit 26 participants with SCI for Project A admitted to IRF (average 8–10 days post-injury). Project B will include participants continuing from Project A as well as additional eligible participants recruited post-discharge. A sample size calculation was performed using G*power software [59] with power set at 0.80 and α at 0.05. We conducted the power analysis based on one SCS study for BP control assessed by head-up tilt test with and without eSCS (n = 4, cervical motor-complete AIS A or B) [33]. A minimum sample of 11 participants is required to detect a significant change in systolic BP during head-up tilt test (mean systolic BP change between stim-off and stim-on = 16.2 ± 12.6 mmHg, effect size = 1.29). Considering a potential 20% dropout rate [60], we aim to recruit 13 individuals with SCI to each group, for a total of 26 individuals with SCI.

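### The article's stratification examples are demographic and its Aim 2 model adjusts only for baseline values, so injury level and AIS grade are neither balanced nor adjusted for at 13 per arm

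*Protocol article*

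**What the plan says.** The only statement on stratification is in the Recruitment section: "We aim to stratify participants based on relevant biological variables (e.g., age and sex". The sentence goes on to give its purpose, which is to "secure a balanced representation of diverse demographic groups, thereby increasing the generalizability of our findings". Just before it, the section says "To control the effect of age, we will use 65-year-old cut-off".

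Eligibility (Table 1) is broad in injury terms: "SCI (non-progressive) at or above the T6 spinal segment" and "American Spinal Injury Association Impairment Scale (AIS) A or B, or C for SCI". The Background gives the rationale for the level criterion: "Injuries at or above the level of sixth thoracic spinal cord segment (≥T6) disrupt descending supraspinal sympathetic control". The Recruitment section repeats it: "Cardiovascular dysfunction becomes particularly prominent at neurological levels ≥T6". The effect size in the Sample size section comes from a much narrower group: "n = 4, cervical motor-complete AIS A or B".

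For Aim 2, the Statistical analysis section compares sham with tSCS after the five inpatient sessions. It uses linear mixed models with time and group, adjusted for baseline values. The natural reading is the baseline value of each outcome. Neither neurological level nor AIS grade is named anywhere in the article as a stratification factor or a covariate.

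**The concern.** The article says which kinds of variable it has in mind for stratification, and they are demographic. The features that set its participants apart as spinal cord injury patients, level and completeness, appear in the eligibility criteria but in neither the stratification examples nor the stated model. The trial population is also more mixed than the four people behind the effect size, since it adds upper thoracic and AIS C participants.

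With 13 per arm, a sizeable chance difference in injury mix is quite possible. If the injury factor predicts later recovery or response to stimulation, adjusting for the baseline outcome removes only the part that acts through baseline BP. Timing may weaken even that: participants enter on average 8 to 10 days after injury, and the Background says neurogenic shock lasts days to weeks. Baseline BP may therefore be a poor guide to the underlying injury (an inference; the article does not say so). At stake is how far the Aim 2 estimates of orthostatic BP, dysreflexia and ADFSCI can be read, and carried forward to the design of a later trial.

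**Working it through.** **1. The plan's own figure.** Inputs from the Sample size section: change 16.2 mmHg, SD 12.6 mmHg, alpha 0.05, power 0.80. Effect size d = 16.2 / 12.6 = 1.286 (stated as 1.29). A two-sample t-test, two-sided, with noncentrality d × √(n/2), gives power 0.776 at n = 10 per group and 0.818 at n = 11. The stated 11 therefore reproduces as a per-group number. With 20% added, 11 × 1.2 = 13.2, in line with the planned 13 per arm. The point below does not change this sample size.

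**2. Chance imbalance on one two-level injury factor.** Let K of the 26 participants have the trait (for example AIS C, or upper thoracic level). The case mix is not in the article, so K is an assumption. Under 13:13 allocation with no balancing on the factor, the number x with the trait in one arm is hypergeometric:

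P(x) = C(13, x) × C(13, K − x) / C(26, K)

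For K = 8, a split of 6 v 2 or worse has probability 2 × (133,848 + 22,308 + 1,287) / 1,562,275 = 0.202.

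| K of 26 (assumed) | Splits counted | Smallest gap counted | Probability |
|---|---|---|---|
| 6 (or 20) | differ by 4 or more | 4/13 = 31 points | 0.160 |
| 8 (or 18) | differ by 4 or more | 4/13 = 31 points | 0.202 |
| 10 (or 16) | differ by 4 or more | 4/13 = 31 points | 0.226 |
| 13 | differ by 5 or more (odd gaps only) | 5/13 = 38 points | 0.115 |

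The range is about 12% to 23%. For two such factors, assumed independent, the chance that at least one shows such a gap is 1 − (1 − 0.115)² = 22% with K = 13 for both, and 1 − (1 − 0.202)² = 36% with K = 8 and 18.

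**3. What such a gap does to the estimate.** Assume the two injury groups differ by 5 to 10 mmHg in recovery; the article gives no figure. A gap of 4 participants then shifts the arm difference by (4/13) × 5 = 1.5 mmHg to (4/13) × 10 = 3.1 mmHg.

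**4. Scale.** Taking the planning SD as the SD of the outcome, the standard error of an arm difference at 13 per arm is 12.6 × √(2/13) = 4.9 mmHg. The shift is 1.5/4.9 = 0.3 to 3.1/4.9 = 0.6 of a standard error. Against the planned effect it is 1.5/16.2 = 9% to 3.1/16.2 = 19%.

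**5. Room for strata.** Level × AIS (two levels each) gives 4 cells, or 26/4 = 6.5 participants per cell. Age × sex × level × AIS gives 16 cells, or 26/16 = 1.6 per cell. Crossing everything is not workable, so one factor has to be chosen.

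**The case against.** Several stronger readings are tempting, and the article does not support them.

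- **Age and sex as the fixed randomisation strata.** A reader might infer this. But the sentence is in the Recruitment section, states an aim, gives age and sex as examples and has representation as its purpose. It does not mention allocation. An article may also leave sequence generation and blocking to the full protocol, so their absence is no finding.
- **Age cut-off versus age stratification.** This is not a contradiction: participants aged 18 to 65 still vary in age.
- **The protocol ties BP control to AIS grade.** It does not say so. The explicit tie is to level, mainly as a T6 threshold that every participant meets. The relevance of AIS grade is inferred from the rationale of lost descending control and from the motor-complete source sample.
- **The comparison is confounded.** That is too strong. Randomisation keeps it unbiased on average, the ordinary standard error carries chance imbalance, and the planned baseline comparisons would probably show a large gap. Project A is a pilot with feasibility outcomes first and between-group autonomic results labelled exploratory.

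The size is also modest. The shift rests on two assumptions (case mix and recovery difference) and stays below one standard error. For K = 8, the 20% chance counts both directions, so about 10% favours either arm.

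What survives is narrower. No stated step balances or adjusts for level or AIS grade, and the stated baseline adjustment cannot absorb an imbalance acting on later recovery or response. Seeing an imbalance in a baseline table after the fact is a weaker remedy than a covariate named in advance, because the choice to adjust would then depend on the data.

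**Conclusion.** The point holds as a limited, low-cost improvement to the Aim 2 analysis. It is not a flaw that invalidates the trial. Eligibility is wide in level and AIS grade, and the article neither balances nor adjusts for them. At 13 per arm the chance of a gap of 31 points or more on one such factor is about 12% to 23%, for an assumed 6 to 20 of 26 participants with the trait. A gap of 4 participants moves the estimate by about 1.5 to 3.1 mmHg if recovery differs by an assumed 5 to 10 mmHg, against a standard error near 4.9 mmHg. The consequence is added variance and a result that is harder to interpret, not systematic bias. The sample size is unaffected. If the full protocol or an analysis plan already names an injury factor for allocation or adjustment, the article only needs to say so.

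**What to change.** **Main change (Statistical analysis, Aim 2).** Prespecify one two-level injury covariate in the linear mixed model alongside the baseline outcome value: AIS A/B versus C, or cervical versus T1–T6. Both come from the baseline ISNCSCI, so no new data are needed. The documents do not decide between the two. The choice can rest on the pooled case mix, and should be written down before outcomes are looked at by arm.

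**Clarification (Recruitment).** State whether the stratification applies to randomisation or only to monitoring who is recruited. If it does apply to randomisation, then for participants not yet allocated use the same single injury factor in place of age × sex, and keep age and sex for recruitment monitoring and description. Those already allocated keep their assignment and are handled by the covariate. If allocation is complete or nearly so, the covariate alone is enough.

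**Cost.** About one model degree of freedom. If the allocation list changes, age and sex are balanced by chance only. Recruitment began in December 2024, and the article says important modifications go to the IRB and the DSMC, so a change to allocation carries more administrative burden than the covariate does.

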### Transcutaneous Spinal Cord Stimulation (tSCS)

A portable tSCS device (SCONE and TESCoN, SpineX Inc., USA, ARC-EX, ONWARD Medical, Netherland) will be used to deliver biphasic 1ms pulses with 10kHz carrier frequency at 30 Hz. The device will be selected based on availability. This stimulation paradigm has demonstrated autonomic recovery in our previous studies [41,42,45]. The location of tSCS is predetermined at T11-T12 and L1-L2 vertebral levels. The stimulation intensity will range from 10 to 230 mA, and selecting the optimal therapeutic stimulation parameters will involve the following criteria: 1) a strong but comfortable sensory experience (initial slight tingling at the site of the electrode followed by some pressure or paraesthesia in skeletal muscles), described as a 5–7 on a 10 point Likert scale, 2) a stable systolic BP not more than 20 mmHg above baseline, and 3) without any symptoms of autonomic dysreflexia (i.e., sweating, goosebumps, tunnel vision, headache, etc.). The stimulation will be reduced if any of the above criteria is not satisfied as well if there are visually detectable skeletal muscle contractions. We will use two self-adhesive round electrodes (diameter of 2.0 cm) placed on the skin between spinous processes at the midline over the vertebral column as a cathode, and two rectangular 7.5  ×  12.5 cm self-adhesive electrodes located symmetrically on the skin over the iliac crests as anodes. The tSCS stimulator will be set with an open-loop stimulation using the same intensity throughout the session.

### Sham stimulation

Sham stimulation is designed to control for placebo effects associated with the perception of the intervention. Sham-controlled randomized designs are essential in neuromodulation research because improvements in autonomic function, pain and overall well-being are highly susceptible to placebo effects, participant expectancy, and observer bias [61]. Sham stimulation will be administered at the same anatomical location. Such sham stimulation has been successfully incorporated as the control treatment in previous and ongoing studies [62–64]. We have adapted these procedures to reduce the possibility that participants will be able to determine their group randomization. The intensity of electrical stimulation will be briefly ramped up to a level at which the participants report perceiving the stimulation (i.e., sensory threshold), then ramped down and turned off for the remainder of the intervention.

### Assessments

**Cardiovascular Monitoring.** Cardiovascular adverse events associated with tSCS at rest will be recorded. We will document the frequency and severity of abnormal BP responses, as well as cardiac responses including tachycardia, bradycardia, arrhythmia, and any associated symptoms. Twenty four-hour BP monitoring will also be used to track BP at day and night [65,66]. Participants will maintain a diary documenting daily activities such as sleep and wake, bowel and bladder management, taking medications, eating, and any instances of symptoms of autonomic dysreflexia and hypotension [67]. The monitoring involves wearing a compact digital BP device (Meditech Ltd., Budapest, Hungary), which is connected to a cuff around the upper arm. The device automatically measures BP at regular intervals, typically every 15 minutes during the day and 60 minutes at night. Heart rate variability will also be assessed. Time-domain and frequency-domain analyses will be performed to evaluate sympathetic and cardiac parasympathetic activity [68], in accordance with the European task force heart rate variability guidelines and based on our prior work [69]. Participants will fill out the Autonomic Dysfunction Following Spinal Cord Injury (ADFSCI) questionnaire at each assessment phase [70]. The ADFSCI questionnaire has participants self-report on the frequency and severity of autonomic dysreflexia episodes.

**Continuous Hemodynamic Monitoring During Orthostatic Challenge**. All participants will undergo continuous beat-by-beat BP monitoring and electrocardiography during a sit-up or head-up tilt test performed with and without tSCS to evaluate cardiovascular safety and real-time autonomic responses [71–73]. Orthostatic blood pressure responses are evaluated during transition from a supine to an upright position of at least 60 degrees [74].

**Neurological Function**. The International Standards for Neurological Classification of Spinal Cord Injury (ISNCSCI) [75] is used to determine the sensory and motor levels on both sides of the body, establish the overall neurological level of injury, and classify the completeness of the lesion (complete or incomplete). The ISNCSCI is a validated and standardized method for neurological assessment following SCI. The International Standards to document Autonomic Function after SCI (ISAFSCI) [76,77] provides a standardized framework for assessing key autonomic domains, including cardiovascular, thermoregulatory, sudomotor, bronchopulmonary, lower urinary tract, gastrointestinal tract, and sexual function, in conjunction with the ISNCSCI. The ISAFSCI will be administered at baseline and post-intervention to track changes in autonomic function along with the changes in neurological function.

**Lower Urinary Tract Function.** During each assessment phase, participants will complete a series of validated questionnaires to evaluate lower urinary tract function. These questionnaires include the Neurogenic Bladder Symptom Score [78], International SCI Lower Urinary Tract Function Dataset [79].

**Bowel Function.** Bowel function will be assessed using multiple validated measures. Time needed for bowel movement and the International SCI Bowel Function Dataset, which allows calculation of the Neurogenic Bowel Dysfunction score, [80] will be recorded at each assessment.

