**Fig 2 pone.0347211.g002:**
[figure not shown]
Trial flow and design of Project A. SCI = spinal cord injury. IRF = inpatient rehabilitation facilities. tSCS = transcuntaneous spinal cord stimulation.

In Project A, we propose a pilot RCT with blinding subject and assessor, two-arm sham-control to evaluate the safety and efficacy of tSCS over the lower thoracic and upper lumbar spinal cord segments for cardiovascular function in adults (18–65 years old) with cervical and upper thoracic SCI (≥T6) American Spinal Injury Association Impairment Scale (AIS) A-C during subacute inpatient rehabilitation. We will recruit 26 individuals with SCI, admitted to inpatient rehabilitation facilities (IRF) (average 8–10 days post-injury). We will conduct this study in the University of Washington Harborview Medical Center (HMC).

Eligible participants will be randomly assigned into two groups as follows: One arm will receive sham stimulation for 30–60 minutes for a total of five sessions, during their IRF stay while maintaining intensive rehabilitation (Sham Group, n = 13). A second arm will receive tSCS for 30–60 minutes for a total of five sessions, in IRFs while maintaining intensive rehabilitation (tSCS Group, n = 13). The intervention frequency and duration are constrained due to the inpatient schedule. We will apply tSCS at rest while maintaining conventional physical therapy, occupational therapy and speech therapy to control for the combinatory effect. This study design also controls for the placebo effect by blinding participants, healthcare professionals, and assessors but not researchers who deliver the intervention. We will collect all outcomes over six months, with three assessments, one at each timepoint of IRF admission, post-interventions, and six-month follow-up.

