### Primary outcomes

The primary outcome for Aim 1 is the feasibility of tSCS in subacute SCI. Safety will be evaluated by cardiovascular responses before, during, and after single and repeated tSCS sessions, including changes in systolic and diastolic BP and heart rate, as well as the occurrence and severity of cardiovascular adverse events related to tSCS or study procedures.

The primary outcome for Aim 2 is the feasibility of recurrent tSCS during the inpatient rehabilitation phase (Project A), defined by (1) adherence to the stimulation and assessment protocols, (2) recruitment and retention rates throughout the study period, and (3) the frequency and severity of adverse events related to tSCS or study procedures. These feasibility indicators align with established guidelines for pilot and feasibility trials [81]. In addition, between-group differences in preliminary autonomic and cardiovascular outcomes will be explored following completion of the five-session inpatient phase (Project A). These outcomes include physiological and clinical measures of autonomic and cardiovascular function, such as systolic BP responses during the sit-up test, the frequency and severity of autonomic dysreflexia and orthostatic hypotension during 24-hour BP monitoring, and patient-reported symptoms of autonomic dysfunction assessed using the ADFSCI.

The primary outcome for Aim 3 is the change in systolic BP during orthostatic stress, assessed using the sit-up test or head-up tilt test, measured at baseline, following completion of the intervention, and at six-month follow-up.

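### As written, the orthostatic test exposes the Project A sham arm to active tSCS, which conflicts with the sham procedure and threatens participant blinding

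*Protocol article*

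**What the plan says.** **Assessments, orthostatic challenge.** "All participants will undergo continuous beat-by-beat BP monitoring and electrocardiography during a sit-up or head-up tilt test performed with and without tSCS". The stated purpose is "to evaluate cardiovascular safety and real-time autonomic responses". No arm, project or visit is exempted.

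**Study design and setting (text after Fig 2).** The two arms are described in different terms. For the control arm (n = 13): "One arm will receive sham stimulation for 30–60 minutes for a total of five sessions". For the active arm (n = 13): "A second arm will receive tSCS for 30–60 minutes for a total of five sessions". On masking: "This study design also controls for the placebo effect by blinding participants, healthcare professionals, and assessors but not researchers who deliver the intervention".

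**Transcutaneous Spinal Cord Stimulation.** Active intensity is titrated to a clearly felt level, 5–7 on a 10-point scale, and is then held constant for the session.

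**Sham stimulation.** Current is raised briefly until the participant perceives it, then lowered and switched off. The aim is concealment: "We have adapted these procedures to reduce the possibility that participants will be able to determine their group randomization".

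**Primary outcomes.** The exploratory between-group outcomes of Project A include "systolic BP responses during the sit-up test", events on 24-hour BP monitoring, and the ADFSCI questionnaire. The primary outcome for Aim 3 is the change in systolic BP under orthostatic stress. Neither entry says whether the run with or without stimulation is meant.

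**The concern.** The sham works only if sham participants have no felt reference for what sustained active stimulation is like. If the assessment itself delivers active stimulation to them, they get that reference within the trial and can set it against sessions in which the current goes off after a short ramp.

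Two things are at stake. The first is participant blinding in the only randomised part of the study. The Sham stimulation section itself argues that outcomes of this kind are prone to placebo and expectancy effects, and one of the between-group outcomes, the ADFSCI, is self-reported. The second is the exposure contrast, because an arm meant to receive no sustained stimulation would receive some. Analysis cannot restore blinding that is lost before the post-intervention outcomes are collected.

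A secondary matter follows from the paired runs. A systolic BP response measured with stimulation on reflects an acute effect, while one measured with stimulation off reflects carry-over or recovery. The outcome definitions do not choose between them.

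**Working it through.** This point turns on wording, so the sections are set side by side.

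1. **Who is tested, and how.** Assessments covers all participants, each tested with and without tSCS. Nothing limits the stimulated run to the active arm or to Project B.

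2. **What tSCS means here.** In Study design and setting, one arm receives sham stimulation and the other receives tSCS. The two procedures are then defined under separate headings. In that vocabulary, a run with tSCS is a run with active current. The stated purpose of measuring safety and real-time responses also fits active current.

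3. **Consequence of 1 and 2.** A site following the text literally would give active stimulation to the 13 sham participants during an assessment.

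4. **What a sham participant could compare.**

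| | Active tSCS | Sham |
|---|---|---|
| Level | 5–7 on a 10-point scale | sensory threshold |
| Duration | constant through the session | brief ramp, then off |

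A participant who can feel the electrode site could tell these apart. This conflicts with the participant blinding claimed in Study design and setting and with the concealment aim in Sham stimulation.

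5. **How large.** The inputs for a dose calculation are missing. The text does not give the visits at which the stimulated run takes place, its order relative to the sessions and questionnaires, its length or its intensity. Fig 1, which holds the schedule, is not shown. The known contrast is five sessions of 30–60 minutes of active stimulation against none.

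6. **Which run is the outcome.** The Sample size section uses a stim-off versus stim-on difference: 16.2 / 12.6 = 1.286, stated as 1.29. A two-sided two-sample t-test at α = 0.05 and power 0.80 with d = 1.29 needs 10.49, so 11 per group, which reproduces the stated minimum. That planning effect is an acute on/off contrast, whereas Trial objectives speaks of recovery, which points to the stim-off run. If the outcome were the stim-on run with active current in both arms, the acute effect would be present in both and would largely cancel between them. The two runs therefore answer different questions. The documents give no attenuation figure, so no revised power is offered.

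**The case against.** The strongest reply is that the sentence may not mean what it literally says. The Assessments section serves both projects, and in Project B everyone, including former sham participants, receives active tSCS. The stimulated run might be meant for Project B only, or might use the allocated stimulation in Project A. The text excludes neither reading, but it states neither. The written rule remains one that would expose the sham arm.

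Several stronger inferences are tempting and are not supported:

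- **That the randomised comparison has failed.** A reader might infer this, but the arms would still differ by five full sessions. The primary outcomes for Aims 1 and 2 are feasibility and safety, and the between-group autonomic comparison is exploratory.
- **That sham participants will certainly feel the difference.** Lesions are at or above T6, with AIS A–C, and the electrodes lie at T11–T12 and L1–L2, below the lesion. Some participants may have little sensation there, and the sham ramp is itself meant to be perceived. Unblinding is plausible for those with preserved sensation, but it is not shown for all.
- **That the assessor is unmasked.** A test run identically in both arms does not reveal the arm. The protocol also separates the researchers who deliver stimulation, who are not blinded, from the assessors.
- **That the contamination can be sized by counting exposures.** Such a count would equate a test run of unknown length with a session of 30–60 minutes, at visits the text does not specify.

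It is also fair to say that the full protocol or analysis plan may settle which run feeds Aims 2 and 3, and that Aim 3 is analysed within participants, where sham masking does not matter. That part is therefore a secondary request.

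**Conclusion.** The point holds as a conflict in the text. The Assessments section, taken with the protocol's own use of the term tSCS, has sham participants receive active stimulation during an assessment. Study design and setting and Sham stimulation require that participants be kept unaware of their allocation.

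The consequence is a threat to participant blinding and some contamination of the sham contrast, affecting up to 13 sham participants. It bears mainly on self-reported between-group outcomes. Its size cannot be given.

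The conclusion assumes that tSCS in the Assessments sentence means active current and that the sentence applies to Project A. The blinding consequence further assumes that at least some sham participants can feel the electrode site and have the stimulated run before their last blinded outcome. It deserves correction before more Project A participants are tested, because the remedy is cheap and lost blinding cannot be recovered.

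**What to change.** Reconcile Assessments with Study design and setting and with Sham stimulation by adopting one of two statements for Project A:

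- the stimulated run of the sit-up or tilt test uses the participant's assigned stimulation, so sham in the sham arm; or
- any active stimulated run in the sham arm takes place only after the last blinded Project A assessment, with that assessment named.

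Also state in advance whether the stim-on or the stim-off run supplies the systolic BP outcome for Aims 2 and 3. The stim-off run fits the stated aim of recovery, and the stim-on run can be reported under Aim 1 as the real-time response. If the full protocol already settles this, a cross-reference is enough.

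Recruitment began in December 2024. If sham participants have already had active stimulated runs, record and report how many and at which visits.

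The cost is protocol wording. The loss is the real-time active response of sham participants during Project A, which the active arm and Project B still supply.
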